#### Trial procedure and timeline

An overview of the trial flow and assessment schedule is presented in Fig. 1 and Table 1, respectively. Trial duration for participants comprises 7 months (including 4 months of intervention and 3 months of follow-up period).

**Fig. 1 Fig1:**
[figure not shown]
Trial flow of the LightMood trial

Once the interested participant contacts the study staff, a screening for eligibility will be applied and the patient will receive an explanation about the study conditions, data storage, and data safety. The patient will be included in the study, if inclusion criteria are met and exclusion criteria do not apply and the participant has given written informed consent. Informed consent will be obtained by trained and supervised study personnel. Once the participant is included in the study and the baseline assessment is completed, allocation into one of the following study groups will be applied via randomization: LightMood intervention (experimental group) or TAU (control group). The patients will be informed about their group allocation result and will get access to the LightMood intervention (only the intervention group), which takes 4 months in total. After completing the 4-month intervention, participants receive the post-treatment assessment (intervention group and control group). Furthermore, there is a 1- and 3-month follow-up assessment.

Standardized notifications and reminders are sent to patients to increase the completion rate and reduce the loss to follow-up rate: a notification is sent when an assessment is due and a reminder message is sent 1 week and 2 weeks after the scheduled time of the assessment.

#### Sample size calculation

The calculation of the sample size was performed using the R-package “Superpower” [38]. Our primary hypothesis is that the intervention will be superior in terms of reducing depression symptoms compared to TAU (control group) at T1. To assess the efficacy of the intervention, we will conduct an ANCOVA analysis with the primary outcome variable at T1 as the dependent variable, the group variable (intervention vs. control group) as a between-subject factor, and the individual baseline levels at T0 as a covariate. Subsequently, a mixed ANOVA analysis with the respective measurements (T0–T3) as a within-subject factor and the group variable as a between-subject factor will be used to explore the intervention’s effect at follow-up.

For the sample size calculation, we selected a preferred test power of 1 − *ß* = 0.80. We anticipate a moderate effect size of *d* = 0.5 for the baseline-adjusted comparison between the intervention and control group at T1. Based on previous studies, we expect the correlation between repeated measures to be *r* = 0.5 [39].

According to the power analyses, a total effective sample size of *n* = 98 (49 participants per group) will provide a statistical power of 80.34 for the ANCOVA analysis mentioned above. With the same number of participants, we achieve a power of 95.8 for the mixed ANOVA analysis mentioned earlier, assuming a conservative assumption that the sole difference between the intervention and control group occurs at T1.

Considering a dropout rate of 30% from T0 to T3, based on existing literature on eHealth trials [40], we estimate that 128 participants (64 per group) will be required. This dropout rate includes loss to follow-up.

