### Study design

The study is an online-based study, which is coordinated in the clinic for psychosomatic medicine and psychotherapy, LVR-University Hospital Essen, University of Duisburg-Essen in Essen, Germany. The study comprises a prospective, randomized controlled trial with two parallel arms. The proposed trial incorporates four distinct measurement time points: the baseline assessment (T0) before randomization, a post-treatment assessment (T1), and a 1-month and 3-month follow-up assessment (T2 and T3). Additionally, continuous assessments are planned during the experimental and control intervention (in-treatment assessment); Table 1 gives an overview of the assessment schedule.

**Table 1 Tab1:** Overview of the assessment schedule

Measures	Baseline	In-treatment assessment	End of treatment	Follow-up assessments	Drop-out assessment

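### The stated 95.8% power for the mixed ANOVA at 49 per group does not follow from the plan's own inputs, which give about 71% for the group-by-time interaction

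*Protocol article*

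**What the plan says.** The Sample size calculation section of the protocol article plans two analyses of depression symptoms. The first is an ANCOVA at T1 with the baseline value as covariate. The second is a mixed ANOVA over T0 to T3, with measurement occasion "as a within-subject factor and the group variable as a between-subject factor will be used to explore the intervention’s effect at follow-up".

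The target power is 0.80. The assumed effect is d = 0.5 "for the baseline-adjusted comparison between the intervention and control group at T1", and for the correlation the section says "we expect the correlation between repeated measures to be" 0.5. A total of 98 (49 per group) "will provide a statistical power of 80.34 for the ANCOVA analysis mentioned above".

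For the second analysis it states: "With the same number of participants, we achieve a power of 95.8 for the mixed ANOVA analysis mentioned earlier". The pattern of group differences behind that figure is given in the same sentence, which describes the calculation as "assuming a conservative assumption that the sole difference between the intervention and control group occurs at T1". The Study design section confirms the number of occasions: "The proposed trial incorporates four distinct measurement time points". No significance level is given.

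**The concern.** The mixed ANOVA is given far more power than the ANCOVA at the same sample size, although the assumed group difference sits at one of four occasions and the interaction test spreads over three degrees of freedom. That ordering is surprising at a correlation of 0.5 and calls for a recalculation.

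The stake is how the follow-up result will be read. The Statistical methods section uses this analysis to judge whether effects are sustained. A power of 95.8% implies a type II error of about 4%. If the true figure is about 29%, a non-significant interaction says much less about the absence of an effect than the article suggests.

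**Working it through.** **Inputs, all from the Sample size calculation section except where noted**
- n = 49 per group, 98 in total.
- d = 0.5 at T1 only, so the group differences at T0, T1, T2, T3 are (0, 0.5, 0, 0) in SD units.
- r = 0.5 between repeated measures, taken as equal for all pairs of occasions.
- Four occasions (also in Study design).
- Alpha: not stated; assumed 0.05 two-sided, with 0.10 also tried.

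**Step 1: reproduce the ANCOVA figure.** The noncentrality is (n/2) × d² / (1 − r²) = 24.5 × 0.25 / 0.75 = 8.17 on 1 and 95 df. Treating the covariate as fixed, power is 80.8%. Allowing for chance imbalance in a random covariate (Shieh's method) gives 80.34%, the article's figure exactly. This supports alpha 0.05 two-sided and d on the raw SD scale. If d were already in residual-SD units, the ANCOVA power would be 68.8%.

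**Step 2: the mixed ANOVA with the same inputs.** For the group-by-time interaction:

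λ = (n/2) × Σ(diff_t − mean diff)² / (1 − r), with df1 = 3 and df2 = 3 × (2n − 2).

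- Mean difference = 0.5 / 4 = 0.125.
- Centred differences = (−0.125, 0.375, −0.125, −0.125).
- Sum of squares = 3 × 0.015625 + 0.140625 = 0.1875.
- λ = 24.5 × 0.1875 / 0.5 = 9.19; df = 3 and 288.
- Power = 71.5%. The multivariate test gives 70.1%, and a simulation of 20,000 trials gives 71.4%.

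A power of 95.8% on 3 and 288 df needs λ of about 18.1, roughly twice the value obtained.

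**Step 3: other readings at 49 per group, d = 0.5, r = 0.5**

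| Reading | Power |
|---|---|
| Interaction, alpha 0.10 | 81.2% |
| Single-df contrast of T1 against the other occasions | 85.1% |
| Same contrast, alpha 0.10 | 91.4% |
| Time main effect | 71.5% |
| Group main effect | 12.1% |

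None reaches 95.8%. Changing the inputs would do it (d of about 0.70, or r of about 0.75), but the article states neither.

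**Step 4: where 95.8 could come from.** Two routes land close to it.
- Entering the total of 98 as the number per group: λ = 49 × 0.1875 / 0.5 = 18.38, power 96.2% (multivariate test 95.9%). Exactly 95.8% falls at 96 per group, where λ = 18.0.
- Using a generic f = 0.25 at 49 per group: λ = f² × df2 = 0.0625 × 288 = 18.0, power 95.7%.

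**Step 5: is a T1-only difference conservative?** Interaction power at 49 per group for other patterns at T1/T2/T3, with T0 = 0:

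| Pattern | Sum of squares | λ | Power |
|---|---|---|---|
| 0.5 / 0 / 0 (the article's) | 0.1875 | 9.19 | 71.5% |
| 0.5 / 0.5 / 0.5 | 0.1875 | 9.19 | 71.5% |
| 0.5 / 0.4 / 0.3 | 0.14 | 6.86 | 57% |
| 0.5 / 0.5 / 0 | 0.25 | 12.25 | 84% |
| 0.5 / 0.6 / 0.7 | 0.29 | 14.21 | 90% |

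So T1-only is not a lower bound for the interaction. It equals the fully sustained case and exceeds gradual waning. For the group main effect it is a low case: 12% against 64% under a fully sustained difference.

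**Step 6: sample sizes around the effective one.** With 30% loss from 128, 128 × 0.7 = 89.6, about 45 per group: λ = 22.5 × 0.1875 / 0.5 = 8.44, power 67%. With all 64 per group retained: λ = 12.0, power 83.6%.

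**The case against.** The strongest defence is about consequence. The trial is sized on the ANCOVA, whose 80.34% is right at 49 per group, and the article describes the mixed ANOVA as exploring the effect at follow-up. A wrong figure for that analysis changes neither the sample size nor the primary test. This stands, and it limits the weight of the point.

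Several stronger readings are tempting, but the document does not support them.
- *That the total was entered as the per-group number.* This gives 96.2% rather than 95.8%, and a generic f = 0.25 at the correct 49 per group comes at least as close. Neither cause can be confirmed from the article.
- *That all secondary superiority claims rest on a 4% type II error.* The 95.8 is computed for depression symptoms with d = 0.5 at T1. The article states no power for self-efficacy, quality of life, mindfulness, eating disorder symptoms or BMI.
- *That conservative is wrong without qualification.* It is wrong for the interaction, but defensible for the group main effect. Nor does every loss of effect reduce interaction power: an effect held at T2 and gone at T3 gives 84%.

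The missing alpha might seem to leave room for the stated figure, but 0.10 still gives only 81%. The 67% at about 45 per group is a completers' figure and is not needed for the correction. The waning patterns are illustrations and do not come from the article.

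**Conclusion.** The figure of 95.8% is wrong as written. From the article's own inputs the group-by-time interaction has about 71% power at 49 per group, some 24 percentage points lower (95.8 − 71.5 = 24.3) and below the plan's 0.80 target. The implied type II error is about 29% instead of about 4%.

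This rests on equal correlations of 0.5 across occasions, d = 0.5 on the raw SD scale, and an assumed two-sided alpha of 0.05; the last two are supported by the exact match to the ANCOVA figure. The label conservative does not hold for the interaction. The error is confined to the stated power of the follow-up analysis of depression symptoms.

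**What to change.** In the Sample size calculation section:
- Replace 95.8 with about 71%, say that it refers to the group-by-time interaction at 49 per group, and state the alpha. Optionally add about 67% if only about 45 per group complete.
- Delete the word conservative or limit it. For the interaction, a fully sustained difference gives the same power, and a gradually waning one gives less (for example 57% for 0.5/0.4/0.3).
- Check the original software input, so that the cause is known and the corrected figure comes from the authors' own run.

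The cost is one corrected number and one or two sentences. The stated power becomes less favourable, but no design element, sample size or primary analysis changes.

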**Methods:**

The trial incorporates four distinct measurement time points: the baseline assessment, the post-treatment assessment, and 1- and 3-month follow-up assessments. Furthermore, we implemented in-treatment assessments for both groups. Participants will be randomized into two groups (LightMood intervention vs TAU). The aim is to include 128 participants (64 per group) in the study. Inclusion criteria are patients who are obese, at least 18 years old, with a private Internet access, and with adequate digital literacy and show depression symptoms (PHQ ≥ 10). Exclusion criteria are weekly outpatient individual psychotherapy, obesity surgery within the last year or planned within the next 7 months, no private Internet access, and the prescription of a new psychotropic drug within the last 2 weeks. The primary outcome is the post-assessment reduction in depression symptoms. Secondary outcomes will include the improvement in self-efficacy, quality of life, mindfulness, reduction in eating disorder symptoms, and body mass index (BMI). Furthermore, we expect a positive development of depression symptoms throughout the different time points (T1, T2, and T3) in patients with obesity.

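### The 30% dropout allowance is added to 98 (giving 128) instead of dividing by 0.7 (giving 140), so 128 randomised with 30% loss leaves about 90, not 98

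*Protocol article*

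**What the plan says.** All the relevant figures are in the protocol article under Sample size calculation. The target is set first: "we selected a preferred test power of 1 − *ß* = 0.80". The effect and correlation follow: "We anticipate a moderate effect size of *d* = 0.5 for the baseline-adjusted comparison between the intervention and control group at T1", and "we expect the correlation between repeated measures to be *r* = 0.5". From these the article concludes that "a total effective sample size of *n* = 98 (49 participants per group) will provide a statistical power of 80.34 for the ANCOVA analysis". It adds that the same number gives 95.8% power for the mixed ANOVA over T0 to T3.

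The loss allowance comes next: "Considering a dropout rate of 30% from T0 to T3, based on existing literature on eHealth trials [40], we estimate that 128 participants", given as 64 per group. The article says that this rate already covers loss to follow-up. The abstract repeats the result: "The aim is to include 128 participants (64 per group) in the study".

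No dropout rate to T1 is given, and no other route from 98 to 128 is described. Alpha and sidedness are not stated in this section.

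**The concern.** By calling the 98 effective, the article separates it from the number randomised: it is what should remain after losses. A dropout rate counted from T0 is a share of those who start. The number to randomise is therefore the target divided by the proportion retained, not the target multiplied by one plus the dropout rate. The two forms are close for small rates but differ clearly at 30%.

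The randomised number is the trial's headline design figure. If it does not follow from the stated inputs, a reader of a null result may credit the trial with 80% power that those inputs do not guarantee. No estimate, test or type I error rate is affected. The issue is whether the stated power and the stated sample size agree.

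**Working it through.** **Inputs from Sample size calculation:** d = 0.5; r = 0.5 between repeated measures; target power 0.80; effective n = 98 (49 per group); dropout 30% from T0 to T3; randomised n = 128 (64 per group).

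**Assumed:** two-sided alpha 0.05, and d in units of the unadjusted SD. Together these reproduce the stated power.

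**1. Reproduce the stated power.** Adjusting for baseline shrinks the SD by √(1 − 0.5²) = √0.75, so the standardised effect is 0.5 / √0.75 = 0.577. With n per group, the noncentrality of the t test is 0.577 / √(2/n) on 2n − 3 degrees of freedom. For n = 49:

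- baseline treated as a random normal covariate (noncentrality averaged over chance baseline imbalance): 80.34%, the stated figure exactly;
- baseline treated as fixed: 80.75%.

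There is little slack. At 48 per group the random-covariate power is 79.5%, so 49 is the smallest group size that reaches 80%.

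**2. Reproduce the stated 128.**

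- 98 × 1.3 = 127.4, rounded up to 128; per group 49 × 1.3 = 63.7, rounded up to 64. This matches the article.
- 98 / (1 − 0.30) = 140; per group 49 / 0.7 = 70. This does not match.

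**3. What 128 leaves.** 128 × 0.70 = 89.6, or 44.8 per group. The largest loss that still leaves 98 is 1 − 98/128 = 23.4%.

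**4. Power of the T1 ANCOVA by the share of the 128 without T1 data.**

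| Without T1 data | Left (per group) | Random covariate | Fixed covariate |
|---|---|---|---|
| 20% | 102.4 (51.2) | 82.1% | 82.5% |
| 23.4% | 98 (49) | 80.3% | 80.8% |
| 25% | 96 (48) | 79.5% | 79.9% |
| 30% | 89.6 (44.8) | 76.6% | 77.1% |

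At 30% the loss against the stated figure is 80.3 − 76.6 = 3.7 points.

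**5. The mixed ANOVA.** I took the stated 95.8% at 49 per group as given and solved for the noncentrality it implies, using an F test with 3 and 288 degrees of freedom at alpha 0.05 (assumed). This gives 18.14. Scaled to 44.8 per group it is 18.14 × 44.8/49 = 16.58, and power is 93.9%.

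**The case against.** The strongest objection is about timing. The primary ANCOVA uses T1, at 4 months, while the 30% runs to T3, at 7 months. Loss by T1 may well be smaller, and at 20% the trial would have about 82% power. This stands, and it is why the power statement has to be conditional. It does not rescue the derivation: the article applies the 30% to the very 98 that powers the T1 analysis, and offers no T1 rate that would justify 128.

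Second, dropout is not the same as a missing T1 outcome. Under Study design, a participant who quits, or does not log in for 6 weeks, counts as a dropout, yet might still answer the T1 questionnaire. A CESD-R is also scheduled at the drop-out assessment. So 90 with T1 data is the pessimistic reading. But the text does not say that dropouts still receive T1, and the drop-out CESD-R is not among the imputation variables listed.

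Third, multiple imputation keeps all 128 in the intention-to-treat analysis. The listed predictors are sex, age and baseline measurements. They add little about a dropout's T1 score beyond the baseline value already in the ANCOVA, so they do not restore an effective 98.

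Fourth, 64 per group is also the two-sample t-test size for d = 0.5 (80.1% power). The article, however, derives 128 from 98 and the dropout rate, so this is a coincidence.

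A reader might infer two stronger conclusions: that the trial will miss 80% power, and that the mixed ANOVA is underpowered as well. The documents support neither. The first depends on a T1 loss that is not given. The second is contradicted by step 5: fewer than 98 would remain at T3, but power stays near 94%.

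**Conclusion.** The step from 98 to 128 is an arithmetic error: 30% was added to the target instead of being taken off the number randomised. On the article's own inputs, 128 randomised leave about 90 after 30% loss, and 140 would be needed to leave 98.

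The consequence for the primary analysis is conditional and modest. If the full 30% lack T1 data, power is about 77% instead of 80.34%. If loss by T1 is at most about 23%, the 80% target holds with 128. The power figures rest on two-sided alpha 0.05 and on d in unadjusted SD units; neither is stated, but together they reproduce 80.34% exactly. The mixed ANOVA figure also takes the stated 95.8% as correct.

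**What to change.** Keep enrolment at 128 and restate the figures under Sample size calculation, for example:

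> With 128 randomised, 30% loss leaves about 90 evaluable. If 30% lack T1 data, the primary ANCOVA has about 77% power (d = 0.5, r = 0.5, two-sided alpha 0.05). The 98 needed for 80% are reached only if loss to T1 is at most 23%.

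The sponsor should confirm the alpha and sidedness when adopting this wording. The cost is one corrected sentence and a slightly less favourable stated power. If the sponsor would rather keep the 80% claim at 30% loss, the randomised number becomes 140 (70 per group), 12 more than planned. If the sponsor expects less loss by T1, a stated and justified T1 rate of at most 23% would also support 128.

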#### Randomization, blinding, and allocation concealment mechanism

The study will utilize randomization (specifically, 1:1 block randomization, with 20 participants per block). Randomization will be applied through a standard computer algorithm (automatically after patients complete the baseline assessment) with no engagement of study personal. The allocation sequence was generated by a study-independent data and information technology manager (author CJ) via a standard computer algorithm. Further study personnel is not informed about the allocation sequence. Stratification will not be applied, as it is anticipated that the randomization process will achieve a balance of prognostic factors. Upon enrollment and completion of the randomization process, the participants will be informed via an automatically generated e-mail of their group allocation. In case of any enquiries, the patients are able to contact the study team via phone or e-mail.

Due to the nature of the trial, blinding the patients will not be feasible. However, to ensure unbiased analyses, the assessors and statisticians involved in the primary analysis will be kept blinded to group allocation. There are no intentions to unblind the assessors or statisticians.

The applied central randomization approach (via a standard computer algorithm) as well as the automatic communication (via the computer system) of the group allocation to the patients will ensure concealed allocation.

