### Participant eligibility and recruitment

Participants will be included if they have a BMI ≥ 30, which is the cut-off score for obesity, an age of 18 and higher, high perceived depression symptom (PHQ-8 ≥ 10), adequate digital literacy, and Internet-enabled device. Furthermore, giving informed consent is mandatory. The intervention will be conducted in the German language.

Participants who had a bariatric surgery within the past year or planned within the next 7 months, have weekly individual psychotherapy, have no private Internet access, and had a regulation of a new psychotropic drug within the last 2 weeks will be excluded. Apart from that, there are no prohibitions regarding the utilisation of health services.

Participants are going to be recruited by study personnel. Flyers and posters will be spread in specialized clinics. In addition, information about the study and the involved staff will be presented online via social media (e.g. Facebook) and the study website. If participants are interested, they can use the link or QR code to go to the study website. Interested participants are able to ask questions regarding the study via email and phone and in person.

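### A single fixed block size of 20, published in the article, leaves block ends partly predictable if recruiting staff learn earlier assignments; automation alone does not ensure concealment (low severity)

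*Protocol article*

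**What the plan says.** All under Methods in the protocol article.

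- **Randomization, blinding, and allocation concealment mechanism.** Allocation is by "1:1 block randomization, with 20 participants per block". There is one list: "Stratification will not be applied, as it is anticipated that the randomization process will achieve a balance of prognostic factors". Assignment is triggered "automatically after patients complete the baseline assessment) with no engagement of study personal". A study-independent data and IT manager generated the sequence, and other personnel are not told it. The section concludes that central randomization "as well as the automatic communication (via the computer system) of the group allocation to the patients will ensure concealed allocation".
- **Same section, blinding.** "Due to the nature of the trial, blinding the patients will not be feasible". Assessors and the statisticians for the primary analysis are to be blinded. Participants learn their arm by automatic e-mail and may phone or e-mail the study team.
- **Trial procedure and timeline.** "Once the interested participant contacts the study staff, a screening for eligibility will be applied". Study personnel obtain consent. Both steps come before baseline and randomization.
- **Study design, note to Table 1.** Study personnel contact participants who drop out, if permission was given.
- **Sample size calculation.** "we estimate that 128 participants (64 per group) will be required".

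**The concern.** Concealment has two parts: the next entry must be hidden, and it must not be inferable from earlier entries. The article deals well with the first part. On the second it fixes one block size, prints it, and uses a single list. Anyone who knew the accrued assignments and their order could count within each block and know the remaining places once one arm had its 10.

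The article leaves two channels through which staff may learn assignments: enquiries from participants who know their arm, and contact with dropouts. The stated blinding covers assessors and statisticians. Nothing says that personnel who screen or take consent are kept from accrued allocations.

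At stake is selection before randomization. The primary outcome is a questionnaire score from participants who know their arm, and the ANCOVA adjusts for the baseline score. It would not remove selection on traits such as motivation or expected adherence. A fixed, disclosed block size has no stated advantage to set against this risk.

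**Working it through.** **Inputs from the article:** block size 20 at 1:1 (10 per arm, m = 10), no strata, planned n = 128 = 6 × 20 + 8. The article gives no figure for predictability, so there is none to reproduce. The share of earlier assignments known to staff is an assumption, varied below.

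**1. Complete knowledge, block starts tracked (upper bound)**

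- Certain assignments per full block: 2m/(m + 1) = 20/11 = 1.82, or 9.1%.
- The last place is always certain. At least the last two are certain in 47.4% of blocks, at least three in 21.1%, at least four in 8.7%.
- Over 128: 6 × 1.818 = 10.9. The final part-block of 8 adds none, because neither arm can reach 10. So 10.9/128 = 8.5%.
- Correct guesses per block when always guessing the arm with more places left: m + (2^(2m)/C(2m,m) − 1)/2 = 10 + (1048576/184756 − 1)/2 = 12.34 of 20, or 61.7%.
- Over 128, including the part-block: 78.3/128 = 61.2%, against 50% by chance.

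**2. Partial knowledge** (simulation; each earlier assignment known independently with the given probability; the guesser picks the arm with fewer known assignments so far in the block)

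| Share known | Certain per block of 20 | Correct guesses, fixed 20 |
|---|---|---|
| 100% | 1.82 | 61.2% |
| 90% | 0.64 | not tabulated |
| 75% | 0.11 | 56.9% |
| 50% | 0.001 | 54.8% |
| 25% | essentially 0 | 52.9% |

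Certainty disappears quickly as knowledge falls. Better-than-chance guessing fades more slowly.

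**3. Alternatives at n = 128**

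- *Undisclosed varying blocks*, for example two of 12, four of 16 and two of 20 in random order (2×12 + 4×16 + 2×20 = 128). Correct guesses are 62.7% with full knowledge, slightly worse than fixed 20. They are 54.6% at 75% known and 52.8% at 50% known, both better than fixed 20. The gain comes from removing known boundaries.
- *Big stick*, limit 8 for illustration. Correct guesses are about 52.6% even with full knowledge. Partial knowledge cannot improve on that, and it already lies below the 52.9% that fixed blocks give at 25% known. It is therefore lower at every level shown.
- *Small blocks.* Random 4/6/8 gives about 68% correct with full knowledge. In fixed blocks of 4, 33.3% of assignments are certain.

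**4. Cost in balance.** The average final difference is about 4 participants under big stick, against about 1.6 with fixed blocks of 20. The worst case is 8 (68:60) under either. At 68:60 the variance factor is 1/68 + 1/60 = 0.03137, against 2/64 = 0.03125, a rise of 0.4%.

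**The case against.** The strongest reply is that the article describes sound concealment. The sequence is independent, withheld from staff and applied automatically, and the result goes by e-mail to the participant. No section describes a running list that staff can see. This stands, and it is why the point is conditional.

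The leakage channels are also narrow. Enquiries are optional. Inactivity counts as dropout only after 6 weeks without login. Recruitment of 128 over about 10 months (August 2023 to May 2024, Trial status) is about 12.8 a month if even, so a block fills in about 20/12.8 = 1.6 months, or roughly 7 weeks. Such dropouts surface when their block is nearly or fully closed. Participants also largely set their own place in the queue by when they complete baseline. A block of 20 is long, which already limits certainty. All of this lowers the severity.

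Several stronger readings are tempting but unsupported:

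- *That the last assignments of each block can be deduced.* This needs near-complete knowledge of earlier assignments and their order, which no section gives to staff.
- *That this is an open trial in which the same people screen, consent and take enquiries.* Assessors and statisticians are blinded, and the article does not say these tasks fall to the same individuals.
- *That eligibility is discretionary.* The inclusion list has "adequate digital literacy, and Internet-enabled device" without a cut-off for literacy, but the full protocol may set one, and most other criteria are factual.
- *That type I error is materially inflated.* Steering by an assumed 0.1 to 0.3 SD with complete knowledge gives about 6% to 15%. With 50% known it is 5.2% to 6.6%, and with 25% known 5.1% to 5.6%. No section supports the assumed steering.
- *That missing an exact 64:64 split is a fault.* Since 128 is not a multiple of 20, equality is not guaranteed (probability 0.35), but 64 per group is a target and the power effect is negligible.

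**Conclusion.** The point holds as a low-severity, conditional weakness. The article claims more for automation than automation alone can deliver: it conceals the list, while a fixed and published block size leaves block ends partly predictable to anyone who learns the accrued assignments. The ceiling is about 1.8 certain assignments per block (8.5% of 128) and 61% correct guesses, given complete and ordered knowledge. With half known, certainty is essentially nil and about 55% of guesses are right. The article does not say how much recruiting staff would learn, so the realistic size within this range is unknown. There is no evidence that any allocation has been or would be predicted. The case for acting is that a better rule is available at almost no cost.

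**What to change.** Before recruitment opens (Trial status says it had not), have the independent IT manager regenerate the list in the same system by one of two routes:

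1. **Preferred: a maximum-imbalance (big stick) rule with an undisclosed limit.** It lowers predictability at every level of knowledge shown above. The price is a somewhat larger average final difference, with no material effect on power.
2. **Alternative: large, randomly ordered, undisclosed block sizes summing to 128.** This removes known boundaries, helps under partial knowledge and gives exactly 64:64. It does not lower the guess rate under full knowledge.

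The limit of 8 and the 12/16/20 mix are illustrations; the values used should be chosen by the IT manager and kept from study personnel. Do not move to small blocks.

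In the randomization section, replace the fixed block size with a statement that the restriction details are not disclosed to study personnel. Add that those who screen and take consent cannot see accrued allocations. If recruitment has already begun, that access restriction can still be put in place and stated.

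Cost: one regenerated list and a short text change. No participants or assessments are added, and the planned analysis is unchanged.
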